### Conventional rehabilitation intervention and rTMS intervention

In addition to the routine pharmacotherapy, the three groups of patients will undergo 40 min of conventional rehabilitation, including physical therapy of upper limb function (PT) and daily living ability training (OT), once each day, 5 days a week, for a total of 3 weeks. Moreover, all stroke patients will receive the same dose of other routine rehabilitation treatments such as biofeedback electrical stimulation, acupuncture, and massage for 3 weeks.

For rTMS intervention, ① patients in the cM1-LF group will be treated as follows: 100 sessions of 1 Hz rTMS at 90% resting motor threshold (RMT) to cM1 (at the optimal stimulus point with the largest and most consistent MEP), 10 pulses per session with a 2-s interval between sessions, totaling 1000 pulses (20 min); ② patients in the cPMd-HF group will be treated as follows: 20 sessions of 5 Hz rTMS at 90% RMT to cPMd (2 cm in front and 1 cm in the inner side of the optimal stimulus point of M1), 50 pulses per session with a 50-s interval between sessions, totaling 1000 pulses (20 min) (Fig. 2); and ③ patients in the CON group will be treated with the same parameters as cM1-LF group (including location, stimulation frequency, and time), however, the coil will be placed perpendicular to the surface of the skull to emit the same stimulating sound as the cM1-LF group but without effective stimulation. All patients in the three groups will receive rTMS intervention once a day for 5 days a week, for 3 weeks.

**Fig. 2 Fig2:**
[figure not shown]
Bimodal Balance-recovery Model for rTMS protocols in this study. Bimodal Balance-recovery Model for rTMS protocols in this study. cM1, contralesional primary motor cortex; cPMd, contralesional dorsal premotor cortex; rTMS, repeated transcranial magnetic stimulation; RTM, resting motor threshold

If any patients experience headaches, nausea, or changes in their condition throughout the interventions, we will terminate the interventions and provide timely medical assistance. Adverse events will also be reported to the ETHICS committee.

### Outcome measures

All patients will receive clinical function assessment, electrophysiological measurement, and multimodal fMRI scanning at all time points. Healthy subjects will only receive fMRI scanning scan at T0. The outcome measure timing is listed in Table 2.

**Table 2 Tab2:** Outcome measure timing

Groups	cM1-LF, cPMd-HF & CON group			HC group		
Time point	T0	T1	T2	T0	T1	T2
Clinical function assessment	○	○	○			
Electrophysiological assessment (MEPs, RMT)	○	○	○			
MRI scan	○	○	○	○		

#### Clinical function assessment and electrophysiological assessment

Clinical function assessment and electrophysiological measurement will be performed at T0, T1, and T2 in Huashan Hospital, Fudan University. The level of motor function will be assessed based on the Brunnstrom stage. Manual muscle test (MMT) and modified Ashworth scale (MAS) will be used to assess muscle strength and muscle tone of the limbs, respectively, whereas the national Institutes of Health Stroke Scale (NIHSS) will be used to assess the severity of neurological deficits in stroke. In addition, Fugl-Meyer Upper Limb Motor Function Rating Scale (FM-UL), Action Research Arm Test Scale (ARAT) and Wolf Motor Function Test Scale (WMFT) will be used to assess the motor function of the affected arm and hand. Activities of daily Living (ADL) will be evaluated using the Modified Barthel Index (MBI).

For electrophysiological evaluation, single-pulse TMS (YRD CCY-4, Yi Ruide Company, Wuhan, China) will be used to assess bilateral hemispherical MEP using a 8-figured coil with an external wing of 7 cm. We will first determine the optimal stimulus point, the location on the scalp with the largest and most consistent MEP in the contralateral Abductor Pollicis Brevis (APB), from which the subsequent neurophysiological assessments will be performed. The resting motor threshold (RMT), which is the minimal stimulus intensity required to evoke MEPs with amplitudes of ≥50 μV in at least five out of 10 consecutive trails, will be determined as the amplitude reference. MEP amplitude and latency, i.e., the peak to peak amplitude and the time period between stimulation onset and start of the largest MEP, will be measured and recorded. In instances where MEP will be recorded in the affected-side APB, it will be denoted as MEP (+), and if multiple measurements fail to yield a MEP, it will be denoted as MEP (−).

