#### Group-level analysis

All statistical analyses will be performed using SPSS software (SPSS 25.0, SPSS Inc., Chicago, Illinois). The intention-to-treat principle will be used for the analysis of functional and electrophysiological data. One-way analysis of variance (ANOVA) will be used to compare the demographic characteristics and baseline assessment (T0) of all outcomes among groups. To compare the treatment effects of different rTMS protocol, a two-way mixed design ANOVA with between-subject factor “Group” and within-subject factor “Time” will be performed for the clinical and electrophysiological changes. Moreover, Bonferroni correction will be employed for post hoc multiple comparisons. *P* < 0.05 will be considered statistically significant for all analyses.

For rs-fMRI and DTI data, a two-way mixed design ANOVA will be performed, with between-subject factor “Group” and within-subject factor “Time” on the data generated in the data processing step, including Eg, El, network betweenness, clustering coefficient, and FA AI. For tb-fMRI data, a whole brain paired T-test will be performed between the task state blocks and baseline blocks in the FC group, and the voxels whose t value is higher than the threshold will be regarded as the activated brain region. For cM1-LF, cPMd-HF, and CON groups, a two-way mixed design ANOVA, with between-subject factor “Group” and within-subject factor “Time” will be performed within the former activated brain region. The most significant point of “Group” × “Time” effect in the activated brain region will be used as the center to construct spherical balls with a radius of 6 mm, and the spherical balls will be regarded as the ROIs. Finally, to obtain the effective connectivity of each patient at different time points, the average time series of all voxels in each ROI will be subjected to dynamic causal model (DCM) analysis.

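### MEP latency, and on the natural reading MEP amplitude, is taken from the single largest response; a mean over a fixed number of trials would be more precise at almost no cost

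*Protocol article*

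**What the plan says.** All points below are from the protocol article.

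- *Clinical function assessment and electrophysiological assessment* defines MEP amplitude and latency in one clause: "the peak to peak amplitude and the time period between stimulation onset and start of the largest MEP, will be measured and recorded". No mean over trials is mentioned.
- The same section defines the resting motor threshold (RMT) as "the minimal stimulus intensity required to evoke MEPs with amplitudes of ≥50 μV in at least five out of 10 consecutive trails" and says that it "will be determined as the amplitude reference". It gives no intensity for recording the MEPs.
- The stimulation site is "the location on the scalp with the largest and most consistent MEP in the contralateral Abductor Pollicis Brevis (APB"). That is a rule for choosing the site and does not by itself settle how responses are summarised afterwards.
- On timing: "Clinical function assessment and electrophysiological measurement will be performed at T0, T1, and T2". Table 2 (*Outcome measures*) lists MEPs and RMT together at all three visits.
- *Group-level analysis* says that a mixed ANOVA with Group and Time "will be performed for the clinical and electrophysiological changes". *Correlation analysis* relates electrophysiological parameters to MRI and clinical scores in the two active groups.

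**The concern.** The article states its readout explicitly, and the readout is an extreme value. A maximum has two drawbacks that the mean of the same trials lacks. It varies more from session to session with excitability unchanged, and its expected value grows with the number of pulses examined. With 20 patients per group (14 if the assumed 30% dropout occurs: 20 × 0.7), avoidable measurement noise widens the error term of the Group × Time test on MEP measures and weakens the correlations. *Aims and hypotheses* names electrophysiology, beside multimodal fMRI, as a means of explaining the mechanism, so these analyses carry weight although the trial is not sized on them.

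A second matter is the phrase about RMT as amplitude reference. It could mean that MEPs are recorded at RMT, or only that stimulus intensity is expressed relative to it. The two readings have different consequences for what an amplitude change can show.

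**Working it through.** The plan gives no figure for MEP variability, so there is none to reproduce.

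**Inputs.** From the article: the largest MEP is read; the RMT rule uses 10 trials, 50 μV and at least 5 successes; there are three visits. Assumed, because the article does not give them: log-normal trial amplitudes with mean 1 and trial CV of 0.4, 0.6 or 0.8; 5, 10 or 20 pulses; independent trials.

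**Step 1: within-session noise.** The log SD is s = √ln(1 + CV²), which gives 0.385, 0.555 and 0.703. The CV of a 10-trial mean is CV/√10. The distribution of the maximum comes from 200,000 simulated sessions per setting.

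| Trial CV | CV of 10-trial mean | CV of largest of 10 | Ratio of squared CVs |
|---|---|---|---|
| 0.4 | 0.126 | 0.241 | 3.6 |
| 0.6 | 0.190 | 0.360 | 3.6 |
| 0.8 | 0.253 | 0.476 | 3.6 |

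At CV 0.6, for example, (0.360/0.190)² = 3.6. The ratio hardly depends on the assumed CV.

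**Step 2: total variance.** Session-to-session or patient spread adds the same log variance t² to both summaries. The ratio becomes (V_max + t²)/(V_mean + t²), where V is the within-session variance of the log summary.

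| Trial CV | V_max | V_mean | t = 0.3 | t = 0.6 |
|---|---|---|---|---|
| 0.4 | 0.051 | 0.016 | 1.33 | 1.09 |
| 0.6 | 0.106 | 0.035 | 1.57 | 1.18 |
| 0.8 | 0.170 | 0.061 | 1.73 | 1.26 |

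For CV 0.6 and t = 0.3: (0.106 + 0.09)/(0.035 + 0.09) = 1.57. The realistic penalty is thus about 1.1 to 1.7 in total log variance. Stable differences between patients drop out of the Group × Time test, so visit-to-visit spread is the t that matters there.

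**Step 3: dependence on pulse count.** The expected maximum, relative to a true mean of 1, is:

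| Trial CV | 5 pulses | 20 pulses | Rise |
|---|---|---|---|
| 0.4 | 1.50 | 1.95 | 30% |
| 0.6 | 1.75 | 2.53 | 44% |
| 0.8 | 1.99 | 3.12 | 57% |

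This matters only if the count differs between visits, which the article does not say. The expectation of the mean is 1 throughout.

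**Step 4: what the RMT could do.** With per-trial success probability p, the chance of at least 5 successes in 10 is 0.50 at p = 0.45 and 0.62 at p = 0.50. The typical response at RMT is therefore close to 50 μV by construction. *If* MEPs were recorded at the RMT found afresh at each visit, a simulation (assumed log SD 0.75, slope 0.12 log units per 1% of stimulator output) puts the median largest of 10 at 126 to 127 μV for log excitability shifts from −0.4 to +0.69. The RMT moves from 51.7% to 42.6% of output. Amplitude would be held nearly constant, and RMT would carry the signal.

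These simulations concern amplitude; no size was computed for latency.

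**The case against.** Four objections have force.

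1. *The sentence is loosely built.* The words about the largest MEP attach securely only to latency. That stands as a caution. Yet the clause names no other response for amplitude, and an average is mentioned for neither measure, so the natural reading covers both.

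2. *An article condenses its protocol.* The number of trials and the recording intensity may be in the full document, and their absence here is no finding. This is right. It also removes a tempting inference, that amplitude is pegged to 50 μV at every visit. No recording intensity is stated, so that cannot be asserted; and even at RMT the simulated largest of 10 lies near 126 μV. What remains is the readout that the article did choose to state.

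3. *Nothing shows that pulse counts vary.* A reader might take "if multiple measurements fail to yield a MEP, it will be denoted as MEP" (−) as evidence of an open-ended count. It concerns only when an affected-side response is called absent. With a constant count the maximum does not drift, so the 30 to 57% rise is a hazard and not an expected error.

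4. *The importance is limited.* With a constant count, a maximum that exceeds the mean by a constant factor does not bias a group comparison, and *Blinding* keeps patients, assessors and statisticians unaware of the assignment. The sample size rests on the Fugl-Meyer score, and RMT is already measured at each visit. All of this stands and confines the point to precision.

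**Conclusion.** The point holds as one of measurement precision. The article reads latency, and on the natural reading amplitude, from the largest MEP. For amplitude at 10 trials this gives about 3.6 times the within-session squared CV of the mean, and about 1.1 to 1.7 times the total log variance once an additional log SD of 0.3 to 0.6 is allowed for. Those figures rest on independent log-normal trials with a CV of 0.4 to 0.8, none of which comes from the article; the direction does not depend on the exact values.

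The affected analyses are the electrophysiological Group × Time ANOVA and the correlations. A reader might infer bias between the groups or a threat to the main clinical result. The documents support neither: assessment is blinded, and the Fugl-Meyer score does not use the MEP. Nor do they make MEP amplitude the decisive test of inhibition against facilitation, since the aims name electrophysiology together with fMRI. The change is worth making because it is cheap, not because the trial fails without it.

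**What to change.** Replace the definition in *Clinical function assessment and electrophysiological assessment* with wording such as: MEP amplitude is the mean peak-to-peak amplitude, and MEP latency the mean onset latency, over a fixed number of consecutive assessment trials (for example 10, the number already used for RMT), the same number at T0, T1 and T2.

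Add one sentence saying what the amplitude reference means. If MEPs are recorded at each visit's own RMT, say so, and read change in excitability from RMT, which Table 2 already lists at every visit, instead of from amplitude.

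The cost is two sentences and at most a few more single assessment pulses per visit. Recruitment began in January 2020, so some patients may already have been assessed; their values can be re-averaged only where the individual traces were stored. The change concerns assessment pulses only and leaves the rTMS treatment untouched.

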### Inclusion and exclusion criteria

A total of 60 eligible patients will be recruited from Huashan Hospital, Fudan University. The inclusion and exclusion criteria are listed in Table 1.

**Table 1 Tab1:** Inclusion and exclusion criteria

Criteria	Description
Inclusion criteria	➤ First-ever stroke ➤ Subcortical stroke diagnosed by head CT or MRI ➤ Clear consciousness and stable vital signs ➤ 18–80 years old ➤ 3–12 months since stroke onset ➤ Unilateral hemiplegia, Brunnstrom stage of affected hand ≤ IV ➤ Right-handed
Exclusion criteria	➤ Severe speech, attention, hearing, vision, sensation, intelligence, mental, or cognitive impairments (MMSE score < 27) ➤ Severe spasticity (Modified Ashworth Spasticity Scale > 2) or pain (Ten-point Visual Analog Scale > 4) of the affected side ➤ Bone, joint, and muscle diseases, other serious nervous system diseases, malignant tumors, and serious heart, lung, liver, and kidney damage ➤ Still enrolled in any rehabilitation or drug studies ➤ Metal implant, magnetic sheet, or cardiac pacemaker ➤ Alcohol or drug addiction ➤ Epilepsy

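### Affected-side MEP latency and RMT have no value when no MEP is evoked, so the named mixed ANOVA keeps only patients who are MEP-positive at every visit, which conflicts with intention-to-treat

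*Protocol article*

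**What the plan says.** The section on clinical function and electrophysiological assessment states that single-pulse TMS "will be used to assess bilateral hemispherical MEP", so both sides are measured. Table 2 places this assessment at T0, T1 and T2. All three measures depend on an evoked response:

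- RMT is the "minimal stimulus intensity required to evoke MEPs with amplitudes of ≥50 μV in at least five out of 10 consecutive trails".
- Amplitude and latency are "the peak to peak amplitude and the time period between stimulation onset and start of the largest MEP".
- For the affected-side thumb muscle, "if multiple measurements fail to yield a MEP, it will be denoted as MEP" (−). No amplitude, latency or RMT value is attached to that category.

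The Group-level analysis section then names a two-way mixed ANOVA, with Group between subjects and Time within subjects, which "will be performed for the clinical and electrophysiological changes". It also states: "The intention-to-treat principle will be used for the analysis of functional and electrophysiological data". The software is SPSS. Neither that section nor the Correlation analysis section names an analysis of MEP (+)/(−) status.

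**The concern.** The plan expects some patients to have no affected-side MEP, because it defines a category for them. It then commits the electrophysiological data to a method that can use only patients with a number at every visit. At a visit without an MEP, latency and RMT do not exist; they are not values that happened to go unrecorded.

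Two things are at stake. First, a patient who is MEP-negative at T0 and MEP-positive at T1 or T2 has regained a measurable corticospinal response, and the latency and RMT analyses would discard that patient. Second, the analysed set is defined partly by what happens after randomisation, so it is not the randomised set that the intention-to-treat statement promises. The electrophysiology is meant to help explain how the stimulation protocols act, so an affected-side result in a selected subset could mislead on that question.

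**Working it through.** **What the plan's own figure covers.** The only sample-size figure is 20 per group, 60 in all, based on FM-UL: 30 rising to 43, SD 17, power 80%, alpha 0.05 (two-sided assumed), dropout 30%. A one-sample (paired) normal formula reproduces it: n = (17 × 2.8016 / 13)² = 13.42, rounded up to 14, and 14 / 0.70 = 20. The documents give no figure for the electrophysiological outcomes and no expected share of MEP-negative patients.

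**Who stays in the ANOVA.** Apply the article's definitions to the possible affected-side histories for latency and RMT:

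| T0 | T1 | T2 | Values available | In a classical mixed ANOVA? |
|---|---|---|---|---|
| + | + | + | 3 | yes |
| − | + | + | 2 | no (MEP returned) |
| + | − | − | 1 | no (MEP lost) |
| − | − | − | 0 | no |

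Other mixed patterns are also excluded. The analysed set is therefore the patients who are MEP-positive at T0, T1 and T2, and two of those three conditions are observed after randomisation.

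The excluded patients raise different problems. A patient negative at T0 leaves because of a baseline value. That alone does not make the arms incomparable, but it narrows the population and removes every return of the MEP. A patient positive at T0 and negative later leaves because of a post-randomisation outcome, and that can make the remaining arms differ.

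A likelihood-based mixed model would keep the incomplete histories. It would do so by assuming a latency or threshold for visits at which neither exists.

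**How many remain (assumption).** Let q be the share of patients without an affected-side value at one visit or more, taken as equal across arms. Complete cases per arm are n × (1 − q), with n = 20, or n = 20 × 0.70 = 14 after the planned dropout (treated as independent of MEP status). The difference between two arms detectable with 80% power is (1.960 + 0.842) × √(2/n), in SD units.

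| q | From 20 | Detectable (SD) | From 14 | Detectable (SD) |
|---|---|---|---|---|
| 0% | 20 | 0.89 | 14 | 1.06 |
| 20% | 16 | 0.99 | 11.2 | 1.18 |
| 40% | 12 | 1.14 | 8.4 | 1.37 |
| 50% | 10 | 1.25 | 7 | 1.50 |
| 60% | 8 | 1.40 | 5.6 | 1.67 |
| 80% | 4 | 1.98 | 2.8 | 2.37 |

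This formula is a normal approximation for one comparison of two arms at one time, and it is optimistic at the smallest sizes. The table describes lost precision. It does not measure the selection after randomisation, which depends on how many patients change MEP status; the documents give no basis for that number.

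**Amplitude.** An absent response can be scored as 0 µV. If it is, the patient has three amplitude values and a returning MEP appears as a gain. The article does not say whether this will be done.

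**The case against.** The strongest reply is that exclusion is inferred and not stated. The article gives no complete-case rule and does not list which electrophysiological variables enter the ANOVA. As a condensed report, it may leave the scoring of a non-response and the tabulation of MEP status to a fuller plan. Part of this stands: a scoring convention for amplitude could sit elsewhere, and its absence here would not be a finding by itself. The reply does not remove the conflict for latency and RMT. The article measures both hemispheres, limits the ANOVA to neither side, and extends intention-to-treat explicitly to these data. No convention for amplitude supplies a latency where there is no response.

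A reader might also infer that most of these severely affected patients would be dropped. The documents do not support that. The relevant severity criterion is "Brunnstrom stage of affected hand ≤ IV", MEP status is not an entry criterion, and no MEP-negative share is stated. A majority is lost only if more than half lack an MEP at some visit, which is unknown.

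A reader might further infer that all electrophysiology, or the trial's main comparison, is compromised. It is not. Contralesional MEP and RMT do not depend on affected-side MEP status. FM-UL, the outcome behind the sample size, and the other clinical scales are untouched.

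**Conclusion.** The point holds for affected-side latency and RMT, and conditionally for amplitude. Followed as written, the analysis of these measures is restricted to patients who are MEP-positive at T0, T1 and T2. It leaves out patients whose MEP returns or is lost, so it departs from the stated intention-to-treat principle.

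This rests on two premises: that affected-side measures enter the ANOVA, as the unrestricted wording implies, and that the ANOVA is the classical complete-data form. For amplitude it also requires that absence is not scored as 0. The size cannot be fixed from the documents. Over an assumed range of 20% to 80% without a value at some visit, 16 down to 4 of 20 per arm would remain. The plan should be changed, but the matter is confined to affected-side electrophysiology.

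**What to change.** In the Group-level analysis section:

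1. Analyse affected-side MEP (+)/(−) at T1 and at T2 by arm, adjusted for T0 status, with exact or penalised logistic regression because the numbers are small. All patients assessed at the visit then contribute, and a returning or lost MEP counts as an outcome.
2. Score affected-side amplitude as 0 when no MEP is evoked, and analyse it by ranks.
3. Report affected-side latency and RMT descriptively, in MEP-positive patients only, and label the results as conditional on an MEP being present.
4. Keep the mixed ANOVA for the contralesional measures.

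The change is to analysis wording and uses data already recorded. Recruitment was still open when the article was submitted, so the change could be specified before unblinding. The cost is slightly more analysis work and the loss of a formal between-arm test for affected-side latency and RMT.
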